## Abstract

**Introduction:**

During the COVID-19 pandemic, general practitioners (GPs) continued to be a main point of contact for patients. For GP practices, it was and still is a challenge to meet constantly changing requirements due to the various phases of the pandemic. The aim of the study is to explore retrospectively the subjective experience with supply and utilization of health care services from the perspective of general practitioners, medical practice assistants and patients, in particular regarding instances of underutilization of services for non-Covid related conditions, adjustments due to the pandemic, and the appropriateness of care.

**Methods:**

The study is carried out within the RESPoNsE research practice network in three of Germany’s federal states: Berlin, Brandenburg, and Thuringia (RESPoNsE—Research practice network east). The study follows a convergent mixed method design, and consists of the following sections: a) two anonymous paper-based questionnaires filled out by GPs and medical practice assistants (MPAs), at an interval of 12 to 18 months; b) in-depth qualitative interviews conducted among a subgroup of GPs and MPAs; c) anonymous paper-based questionnaires among patients of participating practices. The idea for the study was derived from discussions with the practice advisory board of the RESPoNsE network. The themes and issues to be explored in the surveys and interviews are developed and discussed in the practice advisory board, the patient advisory board, and with interested MPAs. The questionnaires will be analyzed descriptively, exploring the effect of demographic variables. Qualitative content analysis is used to analyze the data from the interviews and focus groups.

**Discussion:**

The study focuses on the conditions of GP care during the COVID-19 pandemic. A broad insight is provided as GPs and MPAs, as well as patients, are involved. It provides the opportunity to express needs and concerns. The results can support future discussions on lessons learned from the pandemic and necessary changes in health care delivery.

**Trial registration:**

Trial registration at the German Clinical Trials Register: DRKS00028095.

## Introduction

Primary care plays a crucial role during the COVID-19 pandemic [1, 2].

While hospital care and the concern around potential insufficient intensive care resources were very much a focus in the earlier stages of the pandemic, it was the GP practices who usually (and, again, were) the first point of contact for the patients. Practices often had to decide who needed hospital care; they also provided and monitored patients with COVID-19 at home while providing continuous care for all other patients [3–5].

In Germany, 80 to 85 percent of the patients suffering from Covid-19 received medical care in the ambulatory care sector [6]. Important characteristics of the German health care system as a framework for GP practice organization are described in Box 1.

Box 1. Characteristics of the German health care system as a framework for GP practice organization
Generally
lack of a gatekeeping system;important role of self-governing bodies [7, 8].
General practitioners
are on average responsible for 2,000 inhabitants;see on average 242 patients per week, with an average consultation time of 7.6 minutes;are usually self-employed and work in large part in a single-handed practice;usually rely on a personal communication infrastructure with colleagues, other specialists, and nursing facilities;largely decide autonomously about staff, working hours, and the organization of their practices [7, 9].
Medical practice assistants
(also called health care assistants, or “Medizinische Fachangestellte” in German)work under the legal responsibility of the GPs;go through a three-year vocational training program;are qualified for office and management duties as well as basic clinical tasks, such as measuring blood pressure and taking blood samples;may take over additional tasks including injections, vaccinations, or home visits, according to the “Agreement on the delegation of medical services to non-medical staff in ambulatory healthcare” [10–12].

The pandemic resulted in several spontaneous and unsystematic changes in the supply and uptake of health care services, affecting general practitioners (GPs), medical practice assistants (MPAs), and their patients [13, 14].

The idea for the study protocol presented here was developed in a practice advisory board meeting of the practice-based research network RESPoNsE (for details on RESPoNsE, see Box 2).

Box 2. Context of the study: Practice-based research network “RESPoNsE”“RESPoNsE” is one of six regional practice-based research networks (PBRNs) in Germany funded by the Federal Ministry of Education and Research, comprising practices in three of the 16 federal states in Germany: Berlin, Brandenburg, and Thuringia.These three states together represent 10% of the German population, with the metropolitan area of Berlin and the small- to medium-sized towns and rural areas of Brandenburg and Thuringia, and a medium to below average range of socioeconomic status with regional differences within the federal states [15–17].PBRNs are implemented in many countries and regions to involve primary care practices and patients in identifying relevant research questions [18].RESPoNsE aims to recruit and qualify GPs and MPAs for research activities [19].

GPs and MPAs expressed their view that, although they provided a major portion of COVID-19 patients´care, their worries and issues had rarely been featured in medical journals or the press and were not well-known to the general public. Previous research could show that GPs, from early on in the pandemic, rapidly re-organized their practices, from a fast uptake of virtually-delivered care by use of video or telephone to doctor-led triage [1, 20–25], even though they had to cope with scarce, delayed, or confusing information from public bodies, and were not supplied with sufficient personal protective equipment (PPE) [4, 6, 26, 27]. In 2020, Huston et al. found that preparedness and ability to adapt to the new situation varied between GPs of different countries [28], all of them with a very different health care systems to Germany. Evidence of adaptions in German GP practices is scarce. It is mainly from early phases of the COVID-19 pandemic and is based either on small surveys or on qualitative interviews [29–31].

Reports of a deteriorating work climate in German GP practices also date from early phases of the pandemic [32, 33].

Even though the MPAs in Germany also play a crucial role in meeting the new challenges in German GP practices, there have been only few reports on their perspective from early phases of the COVID-19 pandemic, in which concerns are described regarding the uncertain course of the pandemic, worries and a high level of responsibility for the wellbeing of their patients, fear of contracting COVID-19, and a general feeling of not being properly prepared for the challenges of the pandemic, including the necessary organizational adaptations [34, 35]. While, at the beginning of the pandemic, the focus of public interest and reporting was on the situations of intensive care units and the working conditions for hospital nurses [36], only recently have MPAs received more public attention toward the burden they bore [37].

From the beginning of the pandemic, utilization of health care for non-urgent needs declined [38]. Due to a fear of contracting COVID-19, patients avoided medical care wherever possible [39], sometimes with severe consequences, including death from strokes, heart attacks, cancer, and other acute illnesses [40–42]. A longitudinal online-based patient survey could show that, from the perspective of the patients, the supply of medication has broadly not been impaired, but also revealed that it was considerably more difficult to get an appointment with the GP, with results differing according to which phase the pandemic was concurrently in [43]. In the first six months of the pandemic, in particular, patients postponed regular health checks and routine vaccination appointments [44].

At the same time, mental exhaustion, anxiety, and feelings of loneliness and isolation increased among the general population, adding to the challenges faced by GPs and MPAs during the pandemic [45].

For all three groups, the COVID-19 pandemic may change the general view on the appropriateness of care. Before, there was only limited awareness of unnecessary care [46]. Now (during the pandemic) health care providers, and patients had to decide intuitively and without clear guidance or evidence which medical services were truly necessary [14, 47].

Therefore, the pandemic may also provide the opportunity to revisit health care practices that may not be effective or efficient [13, 48].

It is the subjective experience during the pandemic from the three groups involved (GPs, MPAs, and patients) that most likely will shape the future health care landscape.

Our study will add to the existing evidence by providing:

An up to date view of German GPs, MPAs, and patients on health provision and utilization, appropriateness of care, and the perceived burdens more than two years from the beginning of the COVID-10 pandemic;

An integration and comparison of the views of these three groups;

A participatory approach, involving the three groups already in the development of the study, which, therefore, addresses aspects that were identified as relevant by them;

To our knowledge, no study has been reported that describes the COVID-19 pandemic experiences of all three of these groups (GPs, MPAs, and patients) in Germany, and that addresses organizational adaptation needs, supply, utilization, and quality of care within the GP practices, as well as support needs, and concerns and worries.

### Research framework

Integrating the literature search and discussions with GPs and MPAs, we built our study on the “Covid-19 system shock framework” by Hodgins et al., which identified changes to health services, health workface, information systems, medical products and technologies, funding and finance, health system values and health policy and governance as the main dimensions of relevance to health systems’ responses to the pandemic [49], (Table 1).

**Table 1 pone.0279413.t001:** The COVID-19 system shock framework and themes in the study.

Concepts from the Covid-19 system shock framework	Themes addressed in our study
Changes to health services	Practice organization
	Change of frequency of services
Medical products and technologies	Telephone and Video consultations Protective equipment
Information Systems	
	Supply, usefulness and processing of information
Governance	
	Extra funding for additional work
Funding and Finance	
	Qualification
Health workforce	Stress
	Job satisfaction
	Team spirit
	Responsibility, motivation, and concern
Values	Appreciation
	Appropriateness of care

## Methods

### Aim

This study addresses the following research question:

What are the views of GPs, MPAs, and patients on the provision and utilization of health services during the COVID-19 pandemic? With particular regard to:

aspects of underutilization/undersupply of regular care for non-Covid related conditions;requirements, practicability and sustainability of adjustments to practice organization and management (for example virtually-delivered care); andthe appropriateness of regular care services that may have seemed dispensable under pandemic conditions

Furthermore, the three groups involved (GPs, MPAs, and patients), will have the opportunity to express other aspects or concerns experienced during the COVID-19 pandemic.

### Participatory approach

Using a participatory approach, GPs and MPAs, and patients will play an important role in the PBRN in choosing and prioritizing research topics and in assessing the relevance and feasibility of a research project.

For this purpose, a practice advisory board comprising GPs and MPAs, and (separately) a patient advisory board was founded at the two project centres in Berlin and Jena, Thuringia, to reduce the need for long-distance travel. Research ideas and activities are discussed regularly in the board meetings, enabling participation of the three groups (GPs, MPAs, and patients) at every stage of a project. In our view, it is essential to encourage the participation of all groups who are affected by the research activities and by the potential outcomes.

Serving on a study board or advisory council and attending regular meetings with researchers is one of the most active form of engagement is [50]. In addition to the regular commitments to the practice board by a dedicated group of GPs and MPAs willing to attend regular meetings, all other PBRN GPs and MPAs are invited to visit network meetings, which are held quarterly and provide the possibility to discuss research activities and study ideas.

The Covid-19 pandemic is the focus of this study but also an important factor for the readiness to participate in this particular study and generally in the PBRN:

The pandemic may highlight the importance of research in the primary care setting, as could be shown in an increased interest in research [23]. Therefore, the study will also be combined with a new recruitment effort for the PBRN.

At the same time, research activities may add an extra burden to a practice team that already has reached its limit [51].

Board and network meetings have so far been held via video conference due to pandemic-related restrictions. While this also has the advantage of convenience and saving time—and allows the participation of less mobile patients—it may at the same time exclude patients who are not digitally literate. Being fully aware of these issues, our approach is necessarily pragmatic.

The mode of participation in RESPoNsE is to be seen as consultative to collaborative [52]. While the power for decision-making remains with the research team, due to the accountability owed to the funder, nevertheless we believe that there is “the potential for sharing experience, knowledge and the harnessing of multiple perspectives” [53]. How and when best to involve the three groups will be a learning process that will form part of the structural development of the network, and some fluctuation of level and scope of participation is expected, depending on the context and on individual interests [54, 55].

The idea for this study was derived from discussions in the practice advisory board in May 2020. In order to strengthen the participatory approach, the study has been conceptualized in line with the impressions GPs and MPAs have that some aspects of their work during the COVID-19 pandemic had not yet been addressed adequately: concern regarding the ability to maintain the quality of routine care, a lack of resources (both material and personnel), a constant need for operational responsiveness to changing conditions, a lack of support, and confusing or insufficient information from regulatory and professional bodies. These issues were further discussed in a meeting with a group of interested MPAs, invited via the MPA branch of the Association of Medical Professions (“Bundesverband medizinischer Fachberufe”.) Further aspects of this discussion were new challenges in the area of patient contact (aggressive behavior, for example) and the feeling of a lack of respect from patients and the public, consequentially impacting their job satisfaction.

### Study design and setting

The study will be carried out in three German federal states that are covered by the RESPoNsE network (Berlin, Brandenburg, and Thuringia), comprising approximately eight million inhabitants.

Due to the explorative nature of the study, no sample size calculation was undertaken. Every GP in Berlin and Brandenburg who is statutory health insurance registered (approximately n = 4.100) may take part in the study. The response rate will be a secondary outcome, comparing the rates for GPs who already are part of the RESPoNsE network with those who are not. As other surveys in the Thuringia GP practices are taking place at the same time, only those practices that already are members of RESPoNsE (n = 70) are invited to take part in the study. There are no exclusion criteria.

The GPs have received a postal invitation to take part in the study. MPAs may take part in the study independently of the GPs in the same practice but, as we only have information on the GPs working per practice (and not the MPAs), MPAs will only receive information about the study from the GP who received the letter at their practice.

In line with previous work and similar surveys with GPs, we expect a response rate of about 25% [56, 57]. We expect the response rate to be higher among GPs who are already a part of the RESPoNsE network. As we don`t know how many MPAs are working in the practices we will not be able to calculate a response rate for the MPAs.

The letter to the GPs consists of:

a study information;the questionnaire for GPs (to be filled out anonymously);the questionnaire for MPAs (to be handed out to interested MPAs in the same practice and filled out anonymously by as many MPAs as are willing to take part in the study—the questionnaire be copied if necessary);a prepaid return envelope;a response form (S1 Form), asking for their readiness to take part in the survey or in the further portions of the study (to be filled out with contact details and to be sent back separately via fax or mail);The GPs and MPAs in Berlin and Brandenburg who are not yet members of the RESPoNsE network are also provided with information on network activities and aims and will be asked to express their interest to be part of the network.

After 4 weeks the same letter was sent as a reminder to those GPs who had not yet returned their response form (Fig 1).

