### Quantitatively: Surveys

The questionnaire for GPs and MPAs was constructed and piloted with the participation of the practice advisory board and addresses aspects of routine health care provision during the COVID-19 pandemic, as well as organizational, technical, and staffing measures, external information, and fears and worries about their work environment during the pandemic.

Most of the questions are the same or equivalent for both GPs and MPAs, including information on demographic and professional characteristics (gender, age, location of practice, professional experience). One thematic block varies between the two groups, allowing for a different focus during the preparatory discussions in the meetings with GPs and MPAs. Except for the demographic questions, all the other items are designed on a five-point Likert scale, supplemented by a “don´t know” category where appropriate (Table 3; S2 and S3 Files).

**Table 3 pone.0279413.t003:** Questionnaire for GPs and MPAs (themes, examples, scale).

	Thematic block	Scale
Identical / equivalent to GPs and MPAs	demographic and professional characteristics (gender, age, location of practice, professional experience)	Single choice items
	Changes in frequency for procedures during the coronavirus pandemic (for example scheduled / unscheduled visits, virtually delivered care by use of video or telephone, home visits, routine checks, vaccinations other than Covid-19)	Much less frequent–less frequent–no change–more frequent–much more frequent–don´t know
	*Example statement*: *“How has the frequency for the following service for non-Covid-19 related conditions changed during the pandemic … home visits”*	
	Subjective assessment of the quality of care for chronically ill patients during the corona virus pandemic (for example, changes in quality of care, changes in health conditions of the patients, changes in number of practice visits).	strongly agree–agree—neutral- disagree -strongly disagree -don´t know
	*Example statement*: *“We managed to provide the same quality of care as before”*	
	Personal view on working conditions and job satisfaction during the pandemic (for example, expectations, conflicts within the team, joy at work).	strongly agree–agree—neutral- disagree -strongly disagree
	*Example statement*: *“I am thinking about changing my job”*	

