### Outcomes

The primary outcome is that the views of GPs, MPAs, and patients be obtained, on the supply and utilization of health services during the COVID-19 pandemic, addressing positive as well as negative aspects, such as:

aspects of underutilization/undersupply;possible identification of services that turned out not to be necessary;unanticipated benefits like improvement of organizational matters and use of virtually-delivered care.

Piloting the structural development of the network, secondary outcomes are the number of participating GPs and MPAs and the number of participating patients. The number of participating GPs will be compared in terms of whether or not they are members of RESPoNsE.

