### Data analysis

Data from the returned self-reported questionnaires will be entered manually into a Microsoft Excel spreadsheet and imported into IBM SPSS software (V.28) for data cleaning and analyses. Descriptive statistics (such as frequencies and proportions), summary statistics (such as means with standard deviations or median with interquartile range, as appropriate), and the number of missing values for each variable will be reported. Missing values will not be imputed.

The association of selected demographic and professional characteristics regarding respondents´ views and experiences will be verified with the chi-square test of independence for categorical variables and parametric or non-parametric tests for continuous variables, depending on the distribution. A comparison of GPs´and MPAs´ answers will be performed accordingly. The threshold for significance will be set at 0.05. Multivariate regression analyses will be applied to selected items where appropriate.

Qualitative data from the interviews and focus groups will be analyzed using thematic analyses based on a combined inductive and deductive approach [68]. Data analysis and coding will be facilitated by using the software MAXQDA 2022, release 22.1.1. One author of the multidisciplinary research team will start categorizing and coding the first interviews and develop a coding framework, which then will be discussed with the other members of the research team before being applied to the proceeding interviews.

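### The member versus non-member secondary outcome is a response rate in one section and a head count in another, and neither its region nor its numerator is fixed

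*Protocol article*

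**What the plan says.** Three parts of the protocol article bear on this outcome.

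- **Who is invited** (Study design and setting). For two states: "Every GP in Berlin and Brandenburg who is statutory health insurance registered (approximately n = 4.100) may take part in the study" (the figure is 4,100 in German notation). For Thuringia, because other surveys are running there, "only those practices that already are members of RESPoNsE (n = 70) are invited to take part in the study". Non-members are therefore invited only in Berlin and Brandenburg. The number of members in those two states is not given.
- **What is compared.** Study design and setting makes the response rate a secondary outcome, "comparing the rates for GPs who already are part of the RESPoNsE network with those who are not". The Outcomes section says that "secondary outcomes are the number of participating GPs and MPAs and the number of participating patients", and then: "The number of participating GPs will be compared in terms of whether or not they are members of RESPoNsE". It names no region.
- **What is returned.** The GP questionnaire is anonymous. Under Quantitatively: Surveys, its background items are described as "demographic and professional characteristics (gender, age, location of practice, professional experience"; membership is not among them. The same letter holds a response form with contact details, which is sent back separately. The reminder went to GPs whose form had not arrived.

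The article expects a response of about 25%, and a higher one among members, without a figure for members. For this comparison there is no planned power to check against: "no sample size calculation was undertaken".

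**The concern.** The comparison is meant to inform the development of the network, so a reader will want to know whether members answer more readily than other GPs. Three gaps stand in the way.

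1. An analyst who follows the Outcomes section would compare head counts. Those depend mostly on how many GPs belong to each group, and can point the opposite way to the rates.
2. An analyst who takes all participating GPs, as the Outcomes wording allows, would add Thuringian members to one side with no Thuringian non-members on the other. Any difference in response between Thuringia and the other two states then appears as a difference by membership. The surveys running at the same time in Thuringia are a stated reason why response there might differ.
3. The rate needs a numerator, and two different returns could supply it. On the items listed, only the response form can be split by membership, and the number of forms need not equal the number of questionnaires.

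**Working it through.** **Inputs from the article:** about 4,100 GPs invited in Berlin and Brandenburg; 70 member practices in Thuringia; expected response about 25%.

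**Assumptions:** *m* members in Berlin and Brandenburg, with *m* = 30, 70 or 150; the 70 Thuringian practices counted as 70 GPs; Thuringian response rate *r* of 25%, 40% or 60%. There is no stated figure to reproduce.

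**1. Counts against rates.** Members number *m* + 70 and non-members 4,100 − *m*.

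- Equal 25% response, *m* = 70: members 0.25 × 140 = 35; non-members 0.25 × 4,030 = 1,007.5. The ratio is about 29 to 1 although the rates are the same.
- Response of 60% in members and 25% in non-members (assumed):

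| *m* | Members taking part | Non-members taking part |
|---|---|---|
| 30 | 0.60 × 100 = 60 | 0.25 × 4,070 = 1,017.5 |
| 70 | 0.60 × 140 = 84 | 0.25 × 4,030 = 1,007.5 |
| 150 | 0.60 × 220 = 132 | 0.25 × 3,950 = 987.5 |

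The rates favour members strongly and the counts point the other way. At equal response the counts would match only if 4,100 − *m* = *m* + 70, that is *m* = 2,015, so this result does not hinge on the exact value of *m*.

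**2. Pooling over three states.** Suppose that membership makes no difference in Berlin and Brandenburg (25% in both groups). Then

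pooled member rate = (0.25*m* + 70*r*) / (*m* + 70), and the shift from 25% = [70 / (*m* + 70)] × (*r* − 0.25).

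| *m* | *r* = 25% | *r* = 40% | *r* = 60% |
|---|---|---|---|
| 30 | 25.0% (0) | 35.5% (+10.5) | 49.5% (+24.5) |
| 70 | 25.0% (0) | 32.5% (+7.5) | 42.5% (+17.5) |
| 150 | 25.0% (0) | 29.8% (+4.8) | 36.1% (+11.1) |

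Brackets give the shift in percentage points against non-members at 25%. A Thuringian rate below 25% reverses the sign. The article does not say that this contrast will be tested. If it were tested two-sided at its general 0.05 threshold, the shifts for *r* = 40% and 60% would be flagged with probability 0.36 (*m* = 150, *r* = 40%) to 0.999 (*m* = 30, *r* = 60%). Restricted to Berlin and Brandenburg, the shift is zero under the same assumptions.

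**3. Which return is counted.** Suppose 25% of both groups return the questionnaire, and the form comes from 90% of responding members but only 40% to 60% of responding non-members (assumed). The form-based rates are then 0.25 × 0.90 = 22.5% for members and 0.25 × 0.40 = 10% to 0.25 × 0.60 = 15% for non-members. If both groups send the form equally often, at 90%, both show 22.5% and no difference appears.

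**The case against.** The strongest reply is that the intended analysis can be guessed. Study design and setting says rates, and its sentence on the comparison follows directly on the Berlin and Brandenburg invitation, before Thuringia is mentioned. A rate comparison within those two states is a natural reading. The word for number in Outcomes may be loose phrasing that covers GPs, MPAs and patients together, since the article explains that no MPA rate can be calculated. This is fair, but Outcomes is where an analyst looks for the definition, and it gives the other measure and no region.

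Some stronger readings are tempting, and the documents do not support them.

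- A reader might infer that the comparison is confounded by state as planned. Only a pooled contrast would be. The article does not specify pooling, and the size of any shift rests on assumed rates.
- A reader might infer that anonymity makes membership unknowable. It does not: the response form identifies the GP and already steers the reminder. The questionnaires and the form are supplements that are not shown, so a membership item cannot be excluded. That some respondents send one return without the other is also not documented.
- A reader might infer that Thuringia has no GP denominator because 70 counts practices. The article says the team knows the GPs per practice, so the figure is obtainable and simply not given.
- A reader might infer a failed claim about the effect of membership, or confounded comparisons of views between states. The article claims no causal effect and specifies no comparison between states.

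**Conclusion.** The inconsistency between rate and count holds on the text alone, and the count version is uninformative for any plausible number of members. The pooling problem is conditional. It arises only if the three states are combined, which the Outcomes wording permits and Study design and setting does not clearly exclude. Its size ranges from zero to about 25 points over the assumed values and is unknown in practice. The undefined numerator is a real gap, but its consequence depends on return patterns that the article does not describe. This is an exploratory secondary outcome. The wording should be settled before the comparison is reported, and nothing here touches the views that form the primary outcome.

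**What to change.** - In Outcomes, replace the comparison of numbers with the response rate of Study design and setting, defined once as GPs responding divided by GPs invited. Plain numbers of participating GPs, MPAs and patients can still be reported descriptively.
- Restrict the member versus non-member contrast to Berlin and Brandenburg, stratified by state.
- Report Thuringia's response rate separately, with GPs and not practices as the denominator.
- State whether returned questionnaires or returned response forms are the numerator. If membership is known only from the forms, say that the contrast describes returned forms.

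The cost is a few sentences in two sections and a GP count for the 70 Thuringian practices. The downside is that the contrast loses the Thuringian members. Adding a membership item to the repeat survey would not help: according to Table 2 it goes only to those who took part in the first survey, so it cannot recover first-wave response among all GPs invited.
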